### Statistical methods

#### Primary outcomes

Differences in MAI score, change from baseline to 8 weeks after discharge between the control group and pooled intervention group (MED and MULTI-NUT-MED intervention), will be evaluated by analysis of covariance (ANCOVA). The primary analysis will model the randomization group and baseline MAI-score as independent variables by the intention-to-treat principle. Additional analyses will be adjusted for potential confounders that are unequally distributed between groups despite randomization. Missing data on the primary end point will be accounted for by multiple imputations using the PROC MI procedure with fully conditional specification (FCS) and a minimum of 100 imputations. Imputation will use earlier measurements of the imputed outcome, number of medications, and randomization group, along with age and sex for prediction models.

Differences between mGFR and eGFR based on both the combination of creatinine and cystatin C will be evaluated by mixed linear regression analysis.

The difference in EuroQol-5D-5L score change from baseline to 16 weeks after discharge between the control group and MULTI-NUT-MED intervention group will be evaluated by ANCOVA. The primary analysis will model randomization group and baseline EuroQol-5D-5L as independent variables with either intention-to-treat analysis or per-protocol analysis, where participants are considered compliant if they received and were compliant to at least one intervention if one was recommended, two if two were recommended, two if three were recommended, three if four were recommended, and four if five or six were recommended. Additional analyses will be adjusted for potential confounders that are unequally distributed between groups despite randomization. Missing data on the primary endpoint will be accounted for by multiple imputations using the PROC MI procedure with fully conditional specification (FCS) and a minimum of 100 imputations. Imputation will use earlier measurements of the imputed outcome along with age, sex, and diagnosis codes for prediction models.

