#### Secondary outcomes

The difference in health care costs between the control group and MULTI-NUT-MED intervention group will be evaluated in two stages. In the first stage, the share of participants having zero costs is compared by *t* test or similar. In the second stage, the magnitude of strictly positive health care costs is compared by generalized linear models [144]. Quality-adjusted life-years (QALYs) will be computed based on survival, EuroQol-5D-5L data collection, and Danish preference weights [145]. Incremental cost-effectiveness ratio (ICER) will be computed by dividing the difference in development in health care costs from inclusion to 52 weeks after inclusion between groups with the difference in change in QALYs between groups. The ICERs will be bootstrapped and reported with confidence limits from the bootstrapping, in scatter plots, and in cost-effectiveness acceptability curves.

The difference in AOU score change from baseline to 8 weeks after discharge between the control group and pooled intervention group (MED or MULTI-NUT-MED intervention) will be evaluated similarly to the difference in MAI score change.

DNA sequencing of fecal bacteria will be mapped to an integrated catalog of reference genes of the human gut microbiome in order to generate an operational taxonomic unit. Microbial species and gene diversity (the gut microbiome composition) will be calculated with the Shannon index. Differences in the Shannon index between the control group and intervention group will be evaluated by ANCOVA adjusted for baseline values. Gut microbiome diversity will be evaluated by descriptive analyses in relation to dietary components and nutritional status evaluated by MNA-SF and Global Leadership Initiative on Malnutrition (GLIM) criteria.

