GLIM criteria will be validated against in-depth nutritional assessments performed independently by two blinded and trained nutritional experts (semi-gold standard). The nutritional assessment will include factors related to nutritional status, e.g., dietary intake, factors impeding nutritional intake, appetite, and disease history including LOS and readmissions, body composition, weight history, biochemistry, and physical and psychological wellbeing. The prevalence of malnutrition will be evaluated with descriptive analyses based on specific combinations of phenotypic and etiologic indicators in the GLIM criteria. Finally, statistical agreement analysis between the three malnutrition classifications (MNA-SF, ESPEN, and GLIM) will be evaluated by agreement analysis at admission and up to 16 weeks after discharge. Based on in-depth nutritional assessments, participants only meeting one or two malnutrition classifications will be compared to participants meeting all three malnutrition classifications.

The association between non-GFR determinants and differences between mGFR and eGFR will be evaluated by linear regression analysis. Overall agreement between chronic kidney disease classification based on mGFR and eGFR will be evaluated by Kappa statistics. Results of pharmacogenetic testing including frequency of gene variations and medication interventions based on these variations will be evaluated by descriptive statistics.

Prevalence of frailty will be calculated at baseline and follow-up using three different screening tools (FRAIL, Fried’s frailty phenotype, and FI-OutRef). The effect of the intervention on change in frailty between the baseline and follow-up will be evaluated by mixed models with frailty as the dependent variable and a random effect on participant number, to account for multiple measurements from the same participant. The effect will be measured as an interaction of group and time. Depending on the goodness of fit it may be necessary to categorize frailty. Overall agreement between frailty classification based on the different screening tools will be evaluated by Kappa statistics and mixed models. If the intervention is determined to have a significant effect on frailty, then the agreement between frailty classifications will only be performed using baseline data.

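### As written, the frailty effect is a comparison of change scores that does not adjust for baseline frailty, unlike the trial's ANCOVAs; precision is probably lost, by an amount the protocol cannot fix

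*Protocol article*

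**What the plan says.** The protocol article (Statistical methods, Secondary outcomes) sets the target as "The effect of the intervention on change in frailty between the baseline and follow-up". The method is "mixed models with frailty as the dependent variable and a random effect on participant number", followed by "The effect will be measured as an interaction of group and time". Table 2 lists frailty at baseline, week 8 and week 16, so the baseline value is one of the modelled outcomes. The next sentence leaves the scale open: "Depending on the goodness of fit it may be necessary to categorize frailty".

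Other outcomes are adjusted for baseline:

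- MAI: "The primary analysis will model the randomization group and baseline MAI-score as independent variables by the intention-to-treat principle"
- EuroQol-5D-5L: "The primary analysis will model randomization group and baseline EuroQol-5D-5L as independent variables"
- AOU: to be handled like MAI
- Shannon index: "Differences in the Shannon index between the control group and intervention group will be evaluated by ANCOVA adjusted for baseline values"

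The frailty paragraph names no baseline covariate and no constraint on the baseline means.

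**The concern.** When baseline is an outcome and the groups may have different baseline means, the group-by-time interaction at a visit subtracts the baseline difference in full. Allocation is randomised 1:1, so the expected baseline means are equal. A model that does not use this gives up precision already paid for in data collection. It also leaves the estimate exposed to a chance baseline difference, at a time when patients are acutely ill.

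Frailty is named in the secondary aims, while the sample size was set only for the three primary endpoints. The frailty result also steers another analysis: a significant effect restricts the comparison of frailty classifications to baseline data. A less sensitive test is therefore more likely to let follow-up data affected by the intervention into that comparison.

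**Working it through.** There is no figure to reproduce, because the protocol gives no sample size, power, SD or correlation for frailty. The correlation rho between baseline and follow-up, and the ratio k of baseline SD to follow-up SD, are therefore assumptions shown over a range.

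**Step 1: what the interaction estimates.** With categorical time, a group term at baseline and complete data, the interaction at a visit is the between-group difference in mean change. This was checked on simulated data (130 participants, three visits, random intercept, rho 0.5, equal variances). In 200 fitted mixed models, the interaction at the last visit matched the difference in mean change to within 3e-15.

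**Step 2: variance per participant, follow-up variance set to 1.**

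- Change score: 1 + k² − 2·rho·k
- Baseline-adjusted: 1 − rho²

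With k = 1 these become 2(1 − rho) and 1 − rho². The ratio of adjusted to change-score variance is (1 + rho)/2, and the information lost is (1 − rho)/2.

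| rho | change score | adjusted | ratio | loss |
|---|---|---|---|---|
| 0.3 | 1.40 | 0.91 | 0.65 | 35% |
| 0.5 | 1.00 | 0.75 | 0.75 | 25% |
| 0.7 | 0.60 | 0.51 | 0.85 | 15% |
| 0.9 | 0.20 | 0.19 | 0.95 | 5% |

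**Step 3: simulation check at rho 0.5.** The variance of the ANCOVA estimate divided by that of the change-score estimate was 0.0254/0.0319 = 0.80 over 600 runs. The common-baseline model against the unconstrained model gave 0.0233/0.0289 = 0.81 over 200 runs. Theory gives 0.75, and the differences are within simulation error.

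**Step 4: unequal variances, rho 0.5.** The ratio is 0.75/(1 + k² − k).

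- k = 0.5: 0.75/0.75 = 1.00, no loss
- k = 0.8: 0.75/0.84 = 0.89, loss 11%
- k = 1.25: 0.75/1.3125 = 0.57, loss 43%

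**Step 5: chance imbalance.** With equal variances, a baseline difference of d SD shifts the change-score estimate by (1 − rho)·d in the opposite direction. At rho 0.5 and d = 0.2 SD, the shift is 0.5 × 0.2 = 0.1 SD.

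**The case against.** The strongest reply is that the protocol never says the groups have free baseline means. A model with a common baseline mean is also a mixed model with baseline among the outcomes, and it too reports group-by-time terms. The quoted sentence is compatible with it, and an article may leave parametrisation to the analysis plan. This stands in part: a free baseline mean is the plain reading, not an explicit statement. But the article does name both the model and the effect measure, and on that reading the choice is weaker than it need be.

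Second, the repeated visits justify a mixed model, and the section assigns other repeated measurements to mixed models, so frailty is not an outlier. That is fair, but a mixed model can carry a baseline covariate or a common baseline mean, so repeated measures do not explain the difference from the ANCOVAs.

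Third, the size is uncertain. A reader might infer that a quarter of the information is lost, or that a comparison with 80% power would have about 90%. The documents support neither as fact. The first needs rho 0.5, equal variances and a quantitative score. The second also borrows the 80% that the sample-size section states for the primary endpoints. Baseline is measured in acute illness, so equal variances cannot be presumed, and the plan allows frailty to be categorised.

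Fourth, stratification by age, sex and municipality limits baseline imbalance to the extent that frailty follows those factors. It does not remove the rest.

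**Conclusion.** The point holds as a low-severity improvement to a secondary analysis. On its plain reading, the frailty analysis compares change scores and does not use the equality of baseline means that randomisation provides, while four other outcomes in the same plan are adjusted for baseline.

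A reader might infer that the frailty estimate is biased. It is not: the interaction is unbiased under randomisation and does estimate the stated target. Only precision and sensitivity to chance imbalance are at stake.

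For one follow-up contrast on a quantitative score with equal variances and complete data, the loss runs from 35% at rho 0.3 to 5% at rho 0.9. Outside those assumptions it may be nil or larger, and the documents do not allow a single value to be chosen. Adjustment has essentially no downside, because in large samples ANCOVA with an estimated slope is never less efficient than the change score.

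**What to change.** Keep the mixed model, treat time as categorical, and state one of the following:

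- Constrain the randomised groups to a common baseline mean: group-by-time terms at weeks 8 and 16 only, and no group term at baseline. Let variances differ between visits, because a random intercept alone treats them as equal.
- Model the week-8 and week-16 values with baseline frailty as a covariate.

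The two give nearly the same answer with complete data but can differ when values are missing, so one should be chosen in advance. Report the group difference at each visit. If frailty is categorised, apply the same constraint or covariate in a generalised mixed model.

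The cost is a sentence or two in the analysis plan, with the same data and the same class of model. If a common baseline mean was already intended, one clause saying so settles the point.

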## Methods: participants, interventions, and outcomes

### Overview and trial design

The OptiNAM trial is a single-center block randomized, controlled, observer-blinded, superiority, and explorative trial with two parallel groups. The trial starts upon admission to the ED and includes follow-up visits at 8 and 16 weeks after discharge and a telephone interview at 1 year after discharge in participants with MNA-SF≤11 to collect EuroQol-5D-5L. Figures 1 and 2 and Table 1 provide schematic overviews of the trial design. The trial was initiated on October 15, 2018, and adheres to the Standard Protocol Items: Recommendations for Interventional Trials (SPIRIT) Statement [59]. Trial registration data (Table 1s) and a SPIRIT checklist are provided in the Supplementary material.

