## Methods: data collection, management, and analysis

### Data collection methods

Depending on the outcome, data collection is performed at baseline (t_1_), 8 weeks after discharge (t_2_), 16 weeks after discharge (t_3_), 1 year after discharge (t_1y_), and at the GFR-measurement (t_GFR_) (Tables 1 and 2).

Data collection is performed by the same assessor whenever possible to minimize variation. All assessors are provided supervised training in data collection by primary investigator [name], [name], [name], [name], or [name] until deemed ready to perform data collection unsupervised. Data are collected in the ED at baseline and in each participants’ home during follow-up. If a participant declines full data collection at follow-up, then they are offered minimal data collection consisting of blood samples, body weight, MNA-SF, EuroQol-5D-5L, blood pressure, heart rate, hand grip strength, and body composition with BIA. If the participant declines minimal data collection, then they are offered to complete any components of data collection that can be performed by telephone interview. A full medication list for each participant is recorded at every follow-up visit, and the patient’s diagnosis codes and laboratory tests are accessed in the patient chart and stored for future MAI and AOU scores assessment. A full medication list for each participant is recorded at every follow-up visit, and the patient’s diagnosis codes and laboratory tests are accessed in the patient chart and stored for future calculation of MAI and AOU scores. A self-reported medication list is obtained by a senior pharmacist through interviewing the participant, and this list is cross-referenced with the Shared Medication Card. If there are any discrepancies between medications reported by the patient and those found in the Shared Medication Card, then the senior pharmacist confirms the medications by contacting the participant’s relatives, home care personnel, or GP. Registry data (see Table 2) are obtained retrospectively.

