All additional confirmative outcomes will be evaluated by *t* test, Kruskal-Wallis test, chi-square test, two proportions *z* test, or Friedman’s analysis of variance depending on the distribution of the relevant variable. The analysis will be adjusted for multiple testing. Associations between variables will be evaluated by adjusted multiple regression models, and repeated measurements will be evaluated by mixed models of paired *t* tests or Fisher’s exact test. Missing data on secondary endpoints will be accounted for with multiple imputations as previously described.

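### For the remaining confirmative outcomes the protocol names tests without a baseline covariate, does not settle which analysis gives the treatment effect, and lists Friedman's test, which cannot compare the arms

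*Protocol article*

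**What the plan says.** The final paragraph of Statistical methods, Secondary outcomes, opens with "All additional confirmative outcomes will be evaluated by" and lists five tests: t, Kruskal-Wallis, chi-square, two-proportion z, and Friedman's "analysis of variance depending on the distribution of the relevant variable". It does not say whether follow-up values or changes are tested. Three more statements in the paragraph bear on the point:

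- "The analysis will be adjusted for multiple testing".
- "Associations between variables will be evaluated by adjusted multiple regression models".
- "repeated measurements will be evaluated by mixed models of paired" t tests or Fisher's exact test.

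Other outcomes have their own analysis. MAI and EuroQol-5D-5L use ANCOVA with the baseline value, and AOU is handled in the same way as MAI. For the microbiome, "Differences in the Shannon index between the control group and intervention group will be evaluated by ANCOVA adjusted for baseline values". Frailty has a mixed model with a group-by-time interaction, and health costs have a two-stage model. These are outside the present point.

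The design is a "superiority, and explorative trial with two parallel groups" (Overview and trial design). On timing, "Depending on the outcome, data collection is performed at baseline" and at later visits (Data collection methods). Table 2 gives the visits for each outcome.

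**The concern.** The five listed tests ignore a covariate that is already collected for most of these outcomes. Strength, weight and function vary widely between older acute patients, so chance imbalance at baseline adds noise to an unadjusted comparison. The tests also carry a multiplicity correction, which makes lost precision more costly.

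Friedman's test raises a different problem. It ranks repeated measurements within each participant and has no term for randomised group, so no distribution of the outcome turns it into a comparison of two parallel arms. The Discussion itself says that acutely admitted older patients have a high natural capacity to recover and that the control group is there to separate this from the intervention effect. A Friedman result read as an effect would undo that separation.

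**Working it through.** **Which outcomes are affected (Table 2).**

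| Outcome | Value at t1? | Analysis named |
|---|---|---|
| Grip strength, chair stand, 4-m walk, DEMMI | yes | one of the five tests |
| Functional Recovery Score, WHO-5, body weight, blood pressure, Mini-GDS | yes | one of the five tests |
| Orientation-Memory-Concentration test | yes | one of the five tests |
| Other four cognition tests | no (t2, t3) | one of the five tests |
| ActivPAL | no (starts in first week after discharge) | one of the five tests |
| Dietary intake | no (recorded during hospitalization) | one of the five tests |
| Mortality | no meaningful baseline | one of the five tests |
| AOU | yes | as MAI, i.e. ANCOVA |
| Frailty | yes | mixed model, group by time |

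The t1 value can serve as a covariate: the assessor is blinded, and participants learn their allocation only after baseline data are collected.

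**Does the repeated-measurements sentence settle it?** A mixed model could supply a group effect. A paired t test compares visits within participants, and Fisher's exact test does not handle repeated measurements. The three joined in one phrase do not define a model. Adjusted regression is assigned to associations, not to the comparison of arms. So outcomes measured at t1, t2 and t3 fall under two statements, and neither fixes the treatment-effect analysis.

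**Precision.** The documents give no baseline to follow-up correlation r for these outcomes, so r is assumed. With equal variance s² at both visits, the outcome variance is s² for a t test on follow-up values, 2(1 − r)s² for a t test on change, and (1 − r²)s² for ANCOVA. Hence:

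- ANCOVA against follow-up: 1 − r²
- ANCOVA against change: (1 − r²)/(2(1 − r)) = (1 + r)/2

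The equivalent sample multiple is the reciprocal.

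For power, take the 130 participants with or at risk of malnutrition and the 25% dropout from Sample size: 130 × 0.75 / 2 = 48.75 per group. Choose the standardised effect that gives a follow-up-only t test 80% power at two-sided 5%: (1.960 + 0.842) × √(2/48.75) = 0.567.

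| r | Multiple against change | Multiple against follow-up | Power, change | Power, ANCOVA |
|---|---|---|---|---|
| 0.5 | 1/0.75 = 1.33 | 1/0.75 = 1.33 | 80.0% | 89.9% |
| 0.6 | 1/0.80 = 1.25 | 1/0.64 = 1.56 | 87.9% | 93.8% |
| 0.7 | 1/0.85 = 1.18 | 1/0.51 = 1.96 | 95.1% | 97.5% |
| 0.8 | 1/0.90 = 1.11 | 1/0.36 = 2.78 | 99.3% | 99.7% |

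At a weaker r of 0.3 the multiples are 1/0.65 = 1.54 and 1/0.91 = 1.10.

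**Friedman.** A simulation used 2,000 runs, 48 participants per group, three visits and a within-participant correlation of 0.6. With a time shift of 0.5 SD common to both groups and no group effect, Friedman's test over the three visits rejected in 99.9% of runs. Kruskal-Wallis between groups at the last visit rejected in 4.7%. With no time shift either, the rates were about 5.4% and 4.8%. Friedman's test responds to time, not to allocation.

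**The case against.** The strongest reply is that the list of tests should not be read alone. Most of the affected outcomes are repeated measurements, the paragraph mentions mixed models for those, and frailty shows what such a model might look like. The Aims section also describes group differences in body weight, mobility and other outcomes from admission to follow-up. That suggests change scores, and a t test on change does use the baseline value. Simple tests are proper for outcomes with no baseline, the exact model for each secondary outcome is often left to an analysis plan, and missing secondary data are to be imputed, so the completer count is only illustrative.

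Much of this stands, and it rules out four stronger readings that a reader might infer:

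- That baseline is ignored outright and only follow-up values are compared. The text does not say so, and the aims point towards change, so the 1.3 to 2.8 range cannot be the headline.
- That every other confirmative outcome is affected. AOU, frailty and costs have their own models, and several others have no t1 value.
- That the t and Kruskal-Wallis comparisons are invalid. Under randomisation they are valid. They cost precision and leave chance imbalance uncorrected.
- That Friedman's test is certainly meant for comparing arms. The list is pooled, and within-group description is possible.

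The reply does not remove the point. The protocol does name tests, so this is not mere silence. The mixed-model phrase cannot be carried out as written, and Friedman's test is listed with no limit on its use.

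**Conclusion.** The point holds in a limited form. For the remaining confirmative outcomes with a t1 value, the protocol names tests without a baseline covariate, adds a repeated-measures phrase that is not a coherent model, and so leaves the treatment-effect analysis unsettled. It uses baseline-adjusted ANCOVA elsewhere and gives no reason for the difference. Listing Friedman's test without restriction is an error for any comparison of the arms.

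The loss is moderate: 1.1 to 1.3 times the sample against a t test on change, for an assumed r of 0.5 to 0.8 and equal variances at both visits. The larger figures need the extra assumption that follow-up values alone are tested. None of this touches the three primary analyses.

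**What to change.** Replace the list of tests and the repeated-measurements phrase with:

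- **Continuous outcomes measured at t1:** one between-group analysis, either ANCOVA or a mixed model over t2 and t3, adjusted for the outcome's baseline value and preferably for the stratification factors (age group, sex, municipality). Report the adjusted mean difference with a 95% confidence interval, using a transformation or bootstrap interval where the outcome is skewed.
- **Outcomes without a t1 value** (mortality, ActivPAL, four of the five cognition tests, and dietary intake as recorded): keep simple between-group tests.
- **Friedman's test:** remove it from group comparisons, or limit it explicitly to describing change within a group.

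The cost is a text amendment and analysis programming, best done before allocation is unblinded. No new data or visits are needed.
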